### Primary aims: HIV/AIDS and HIV testing knowledge acquisition and retention (information)

Determine how (Aim 1) short-term improvement and (Aim 2) longer-term retention of HIV/AIDS and HIV testing knowledge varies by information delivery mode (pictorial brochure or video), language (English or Spanish) and health literacy level (lower or higher) per four alternative hypotheses (HAs) (also provided are examples of outcomes of each HA):HA1 (3-way interaction of information delivery mode, language, and health literacy): e.g., improvement and/or retention of knowledge will be greatest among participants in the video arm who are English speakers and have higher health literacy, and will be least among those in the pictorial brochure arm who are Spanish speakers and have lower health literacyHA2 (2-way interaction of information delivery mode with language or health literacy): e.g., improvement and/or retention of knowledge will be greatest among participants in the video arm who are English speakers or higher health literacy patients, and will be least among those in the pictorial brochure arm who are Spanish speakers or lower health literacy patientsHA3 (no interaction with information delivery mode): e.g., improvement and/or retention of knowledge will be greater in the video arm than the pictorial brochure arm regardless of language and health literacy levelHA4 (no difference): improvement and/or retention of knowledge will be the same regardless of information delivery mode, language, and health literacy level (i.e., either a pictorial brochure or a video is useful for all patients)

### Secondary aims: HIV testing motivation, behavioral skills and behaviors

In addition to the information construct from the IMB model assessed in the primary aims, we will examine the IMB model constructs of motivation and behavioral skills, their interrelationships, their impact on HIV re-testing, and the moderating influence of information delivery mode, language and health literacy level on:Motivation: Improved/increased (1) attitudes toward need for HIV testing for oneself, (2) beliefs regarding the value of HIV testing, and (3) self-perceived risk for having an HIV infection;Behavioral skills: Increased skills and perceived self-efficacy on (1) initiating/seeking HIV testing, (2) interpretation and response to HIV test results, and (3) assessment of HIV risk and need for repeat testing;Behavior: Greater (1) HIV testing uptake 12-months post-enrollment when offered in the study, (2) HIV testing not part of the study during the study period, and (3) HIV testing utilization 12-months post- vs. pre-enrollment

#### Exploratory aims

To help apply the findings from our trial to ED practice, we will (1) explore brief, easy-to-use, single-question methods [40–43] that ED non-research staff could use to identify lower health literacy patients who would benefit more from information delivered via video or a pictorial brochure. We will also (2) assess participant satisfaction with their assigned information delivery mode and (3) their self-reported changes in HIV risk-taking behavior over the one-year follow-up period.

## Methods/design

### Theoretical framework of study

The study uses the IMB model (Fig. 1) to guide the selection of constructs and their measurement [34, 35]. Increase in and retention of information (knowledge) is the primary outcome, given that the chief purpose of the video and pictorial brochure is to provide HIV/AIDS and HIV testing information. However, the video and pictorial brochure also aim to increase motivation and improve behavioral skills related to HIV testing. Hence, changes in motivation and behavioral skills also will be measured. Given that HIV testing is a recurring event, especially for those at risk, we will measure the impact of the video vs. pictorial brochure on behaviors, chiefly acceptance of repeat HIV testing 12-months post-enrollment, as well as repeat testing during the study period and change in testing uptake at 12-months post enrollment. The interrelationships among knowledge, motivation, and behavioral skills, and their impact on testing behavior will be assessed. We also will examine the moderating influence of delivery mode, language, and health literacy level.

**Fig. 1 Fig1:**
[figure not shown]
Information-Motivation-Behavioral Skills model as a theoretical framework for the trial

### Study sites and recruitment feasibility

We will conduct the study at four EDs (Birmingham: University of Alabama at Birmingham [UAB] Hospital; Cincinnati: University of Cincinnati Medical Center; Los Angeles: Olive View/University of California Los Angeles [UCLA] Medical Center; and Providence: Rhode Island Hospital) (Fig. 2, Table 1). The four study sites were selected because of their experience in conducting HIV testing research in their EDs, geographic and demographic diversity (permits sub-analyses by demographic characteristics), heterogeneity of HIV prevalence in the referring community, research infrastructure, and high ED patient volumes (enables easier recruitment). At two sites (Los Angeles and Providence), 38 and 15%, respectively, of ED patients only speak Spanish. Accordingly, we plan to recruit Spanish speakers at our Los Angeles and Providence sites, and English speakers at our Birmingham and Cincinnati sites.

**Fig. 2 Fig2:**
[figure not shown]
Participant recruitment feasibility estimates by study site, language, and health literacy level

**Table 1 Tab1:** Descriptions of study sites

Location	Annual ED patient volume	ED patient demography	HIV prevalence
UAB Hospital ED	55,000 visits	• 54% black, 42% white, 3% Latino	• 0.4% in Jefferson County
Birmingham, AL	18–64-year-olds/year	• 53% female, 47% male	• 0.3% seroprevalence among those tested in ED
UCMC ED	83,000 visits	• 51% black, 44% white, 1% Latino	• 0.15% in Cincinnati metro area
Cincinnati, OH	18–64-year-olds/year	• 48% female, 42% male	• 0.4% seroprevalence among those tested in ED
Olive View-UCLA	63,000	• 5% black, 20% white, 70% Latino	• 0.38% in Los Angeles
Medical Center ED	18–64-year-olds/year	• 51% female, 49% male	• 4.4% seroprevalence among those tested in ED
Los Angeles, CA		• 75% of Latinos primarily speak Spanish	
Rhode Island Hospital ED	87,000 visits	• 10% black, 60% white, 30% Latino	• 0.2% in Providence metro area
Providence, RI	18–64-year-olds/year	• 48% female, 52% male	• 0.01% seroprevalence among those tested in ED
		• 50% of Latinos primarily speak Spanish	

We will recruit a total of 1200 patients (600 English-speakers and 600 Spanish-speakers) over a two-year period. The RA at each ED will recruit 300 ED patients over four shifts/week for 48 weeks/year for 2 years (384 shifts total/RA), and devote one shift/week to participant follow-up, training, and administrative duties. To reach recruitment goals, each RA must recruit at least 0.78 patients/shift. In comparison, we recruited 1.25 Spanish-speakers/shift in our previous R21 study (R21NR011997). Our recruitment estimates are conservative and assume that 25% of ED patients are study ineligible (see study inclusion criteria), 50% would decline participation, and only 25% would be classified as lower health literacy. As shown in Fig. 2, ample participants are available for recruitment at each ED per these assumptions.

### Study materials and instruments

#### HIV/AIDS and HIV testing video

“What do you know about HIV and HIV testing?” and its equivalent Spanish-language version “¿Qué sabe usted sobre el VIH y sobre las pruebas del VIH?” [21] is a 15-min animated and live-action video that contains CDC-recommended information about HIV/AIDS and HIV testing [2], as well as additional information about acute HIV infection and current methods of HIV testing (rapid and conventional; oral, fingerstick and phlebotomy sampling; and antibody, antigen, and ribonucleic acid testing) without mention of any type of testing product. The video may be downloaded or viewed without cost at http://biomed.brown.edu/hiv-testing-video/. The content of the video is grounded in the IMB model [34, 35] with a primary emphasis on improving knowledge about HIV/AIDS and HIV testing, while also increasing motivation for testing and improving behavioral skills regarding HIV testing. (See Additional file 1 for details of content according to IMB model components). The voice-over narrated video follows two protagonists (male and female; purposely racially/ethnically ambiguous and not named to appeal to a wider audience and avoid social labels) as they receive information about HIV/AIDS and HIV testing and proceed through the HIV testing process. Animation, graphics, images, still shots, text, and live-action segments emphasize the topics presented. The Fernandez-Huerta Readability Score [44] for the Spanish-language version of the script for the video is 85, which indicates an “easy” level of reading difficulty. The final English-language version of the video script has a Flesch reading ease of 72.9, indicating a low reading ability level (appropriate for 11-year-olds).

#### HIV/AIDS and HIV testing pictorial brochure

The HIV/AIDS and HIV testing pictorial brochure is a compact printed version of the video, “What do you know about HIV and HIV testing?” and its equivalent Spanish-language version, “¿Qué sabe usted sobre el VIH y sobre las pruebas del VIH?” [21] It contains identical information as the video, except there is no voice-over narration, music, animation, or live-action segments. Instead, graphics, images, and still shots of selected components of the animated and live-action segments are depicted. The Fernandez-Huerta Readability Score [44] and the Flesch reading ease are identical to the video. English- and Spanish-language copies of the text of the video and pictorial brochure are in the Additional file 1.

### Study instruments (see Additional file 1 for English-language copies)

Table 2 depicts the study instruments that will be used in the study.

**Table 2 Tab2:** Study instruments description and administration

Instrument	Description	Administration
Screening, eligibility and enrollment questionnaire	• Karliner, et al. Spanish language proficiency & preference [54]	• Baseline
	• Ballard and Tighe Idea Proficiency Test II	• Administered by RA
	• Demographic characteristics & nativity	• < 5 min
	• US acculturation (for Latinos) per the SASH [63]	
	• HIV testing history & HIV-related exclusion screen	
	• Willingness to undergo rapid HIV testing	
	• Adapted from our prior research [19, 21, 45–51]	
Short Assessment of Health Literacy-Spanish & English (SAHL-S&E [22])	• Measures health literacy level	• Baseline
	• Score of ≤14 indicates lower health literacy	• Administered by RA
	• *SAHL-S* is highly correlated with *TOFHLA* (*r* = 0.62), & *SAHL-E* is highly correlated with *REALM* (*r* = 0.94) & *TOFHLA* (*r* = 0.68)	• 3–5 min
	• *SAHL-S&E* reliability is 0.80 & 0.89, respectively	
3 single-item screening tests for health literacy [40–43]	• Derived from the S-TOHFLA	• Baseline
	• AUCs for 3 questions vs. S-TOHFLA (0.66–0.74) vs. REALM (0.72–0.84)	• Administered by RA
		• < 1 min for each question
HIV testing motivation and behavioral skills questionnaire (Behavioral Skills and motivation)	• Measures **Motivation:** (1) attitudes toward need for HIV testing for oneself, (2) beliefs regarding the value of HIV testing, and (3) self-perceived risk for having an HIV infection; and **Behavioral skills:** skills and self-efficacy on (1) initiation/seeking of HIV testing, (2) interpretation and response to HIV test results, and (3) assessment of HIV risk and need for repeat testing	• Baseline (pre- and post-information by video or pictorial brochure)
	• Adapted from our prior research [47, 49, 51] and other author recommendations [74]	• Self-administered by telephone
		• < 2 min
HIV/AIDS and HIV testing information delivery mode preferences and satisfaction questionnaire	• Measures preferences and satisfaction with pictorial brochure or video	• Baseline (pre- and post-information by video or pictorial brochure)
	• Adapted from our prior research [20]	• Self-administered by telephone
	• 1 Pre- and post-information question on preferences with delivery mode	• 1 min
	• 1 post-information question on satisfaction with delivery mode information	
HIV/AIDS and HIV testing knowledge questionnaire [21] (Information)	• Measures HIV/AIDS and HIV testing knowledge applicable to CDC-recommended information at the time of testing	• Baseline (pre- and post-information by video or pictorial brochure)
	• Cronbach’s α = 0.80; *See A.1. Preliminary research for more details about development, testing, and utilization of this instrument*	• 3, 6, 9 and 12-month follow-up
	• 25 questions; yes/no/don’t know responses	• Self-administered by telephone
		• 5–10 min
HIV risk-taking questionnaire	• Measures number of partners and frequency of condom usage by gender and type of partner (main, casual and exchange partners) and injection-drug use	• Baseline
	• Based upon CDC National HIV Behavioral Surveillance System (NHBS)	• 3, 6, 9, and 12-month follow-up
	• Adapted from our prior research [47, 49, 53]	• Self-administered by telephone
		• 5–10 min
HIV test utilization questionnaire	• Queries participants about HIV testing in the follow-up period	• 3, 6, 9, and 12-month follow-up
	• Adapted from our prior research [47, 49, 51]	• Self-administered by telephone
		• < 2 min
Repeat rapid HIV testing acceptance questionnaire	• Measures participant acceptance of offer of repeat rapid HIV testing at 1 year post-enrollment and reasons for acceptance/decline	• 12-month follow-up
	• Adapted from our prior research [47] and research by other authors [49, 51, 75–80]	• Self-administered by telephone
		• < 2 min

### Study preparation (months 1–6): RA hiring and training, study preparation, and brief pilot study

#### RA hiring and training (months 1–5)

We will work with the study site investigators to hire and train RAs at each study site. The project manager, principal investigator (PI), co-investigators, and site investigators will conduct training of the RAs in person through site visits and video conferences. We will ensure that the RAs are adept in screening and enrolling participants and executing the protocol of the trial. As we have done for our prior studies [19–21, 45–51], the RAs also will undergo their respective state-sponsored HIV counseling and testing training, and instruction on rapid HIV testing with the PI and the rapid HIV test manufacturers.

#### Study instrument preparation (months 1–2)

We will prepare our study instruments for each trial site and for the follow-up components. The baseline English and Spanish versions of the enrollment and eligibility screening and health literacy questionnaires will be loaded onto tablet computers for the QDS™ software data collection system (NOVA Research, Bethesda, MD), which we have used in our previous studies [17, 19–21, 45–50, 52, 53]. We also will load our video, “What do you know about HIV and HIV testing?” (English- and Spanish- versions) [21], onto the tablet PCs. Finally, we will prepare the rapid HIV testing data collection and quality assurance forms and protocols we used for our prior studies for each study site [19–21, 45, 47–49, 51, 53].

We considered a variety of methods of administering the remaining questionnaires for the baseline and consecutive three-month follow-up periods. We need a system that is convenient for participants; can be accessed from virtually any location in the US; is available 24 h/day, 7 days/week; is easy-to-use for participants; can deliver the questions in English or Spanish; and is responsive to those with lower literacy skills. Considering these needs, we will use the Database Systems Corporation automated telephone key-pad response system for delivering the questionnaires at baseline and for each follow-up. Participants will be given a toll-free telephone number to call and complete the questionnaires. Participants will use this system at study entry in the ED with the on-site assistance of the RA. In so doing, we will verify that participants know how to use the system. Those participants who are having difficulty with using the system during follow-up will have the option to provide their responses with the assistance of the RA through a telephone call.

#### Brief pilot study (month 6)

We will conduct a brief pilot study to finalize the study protocol. The pilot study will serve to further train the RAs, enable us to “trouble-shoot” the study methods, gather some pilot data to review and ensure accuracy and completeness of the study data, and rectify any problems. For the pilot study, each RA will enroll five participants. Study inclusion criteria and protocol will be the same as for the randomized, controlled trial (provided below).

### Randomized, controlled trial (recruiting months 7–42; follow-up ends month 54)

#### Study inclusion criteria

18–64-years-old (per CDC HIV screening recommendations [1])Speak English or SpanishNegative baseline rapid HIV test (described below)Not enrolled in a conflicting HIV study (described below)Can provide informed consent and can participatePlan to remain in the US for 12 months

#### Enrollment (months 7–42)

The RAs will approach a random sample of ED patients who might be eligible for the study. The random selection process entails a computer-based selection of ED patients to approach, as we have done in our previous studies [19, 20, 45, 47–51]. In brief, this process involves creating lists of ED patient rooms, entering them into the computer-based random selection program (www.random.org), and generating a list of the rooms in random order in advance of each data collection shift. The RA will review the electronic ED medical records of patients according to these lists and determine which patients are potentially study eligible.

The RAs will approach ED patients who appear to be eligible and conduct a further in-person screen of their eligibility. Study screening enrollment and participation will be stratified by language (English or Spanish) (Fig. 3). Ability to read and comprehend English and Spanish at least at a 6th grade level will be verified using the Ballard and Tighe Idea Proficiency Test II Form E for English language and the fourth edition for Spanish language (Ballard and Tighe Publishers, Brea, CA). Patients who self-identify as primarily Spanish speakers also will complete the two-question screener by Karliner et al. [54] to confirm preference for Spanish-speaking in medical settings. Afterwards, they will complete the Spanish-language version of the questionnaires and receive the applicable study materials. Patients who decline or abort screening or study participation at any time will be asked to provide their reasons, which will be recorded in the study database. If the reason can be overcome (e.g., waiting for a radiograph), the RAs will accommodate the request, and will proceed with screening or participation.

**Fig. 3 Fig3:**
[figure not shown]
Trial protocol flow diagram

For those who agree to be screened (verbal consent will be obtained), the RAs will administer the screening, eligibility and enrollment questionnaire (*See* Additional file 1). The screening questionnaire consists of questions about demographic characteristics and HIV testing history. Patients who self-identify as HIV infected or are enrolled in conflicting HIV studies (e.g., HIV vaccine, HIV pre-exposure prophylaxis [PrEP], or a study that measures HIV testing over time or similar outcomes as this study) will not be eligible and will be thanked for their time. Next, the RA will administer the three health literacy questions [40–43]. The RA then will administer the SAHL-S&E [22] to stratify participants by health literacy level (lower or higher). During the course of the latter portion of the study if a participant’s health literacy level exceeds the quota for the study site, he/she also will not be eligible for participation.

#### Pre-information delivery questionnaires

Patients agreeing to participate will complete the pre-information delivery questionnaires with the automated telephone key-pad response system using the RA’s cellular phone. These instruments are the HIV risk self-perception and value of HIV testing, HIV/AIDS and HIV testing information delivery mode preferences, and the HIV/AIDS and HIV testing knowledge questionnaires (See Additional file 1). Verbal consent will be obtained for this portion of the study.

#### Information delivery and post-information delivery questionnaires

We will randomly assign patients in a 1:1 ratio into information delivery mode Arm 1 or Arm 2. As noted previously, the two arms will be stratified within language (English or Spanish) and health literacy level [22] (lower vs. higher) (*n* = 150/stratum). We will use block randomization techniques to ensure that there are equal numbers in each arm per study site and stratum using a centralized, random assignment computerized system. Randomization sequences by language and health literacy level will be posted on a secure website that RAs across all four sites will consult when assigning participants to study arms. The advantage of this approach is that we can monitor enrollment and balance within study arms and across study sites easily, address concerns as they arise, and permit efficient use of study resources. The two groups will differ by the following:Arm (1): HIV/AIDS and HIV testing video: Participants in Arm 1 will watch the video, “What do you know about HIV and HIV testing?” (in English or Spanish) on a tablet computer in the ED while the RA waits. They will listen to the audio components using disposable headphones.Arm (2): HIV/AIDS and HIV testing pictorial brochure: Participants in Arm 2 will be provided with a copy of our HIV/AIDS and HIV testing pictorial brochure (in English or Spanish) to review in the ED. Arm 2 participants will read the brochure while the RA waits. The RAs will not provide clarifications or assistance with the information in the pictorial brochure.

After watching the video or reviewing the pictorial brochure, all patients will complete the post-information questionnaires using the automated telephone key-pad response system (the HIV risk self-perception and value of HIV testing, HIV/AIDS and HIV testing information delivery mode preferences and satisfaction, the HIV/AIDS and HIV testing knowledge, and the HIV risk-taking questionnaires). Patients will receive a re-chargeable gift card for participating.

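### Randomisation sequences are posted for the research assistants who screen and stratify patients, and no stated step hides upcoming arms, so allocation concealment is not assured

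*Protocol article*

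**What the plan says.** In the section on information delivery and post-information questionnaires, the article sets out 1:1 assignment. It promises that blocking will "ensure that there are equal numbers in each arm per study site and stratum", "using a centralized, random assignment computerized system". The next sentence describes what staff work from: "Randomization sequences by language and health literacy level will be posted on a secure website that RAs across all four sites will consult" at the time of assignment. The advantages claimed for this arrangement are easy monitoring of enrolment and balance, and efficient use of resources. Concealment is not mentioned.

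The Enrollment section gives the steps before assignment to the same staff. After reviewing records, "The RAs will approach ED patients who appear to be eligible and conduct a further in-person screen of their eligibility". They give the screening and enrolment questionnaire and the three short literacy questions. Then: "The RA then will administer the SAHL-S&E [22] to stratify participants by health literacy level (lower or higher"). Table 2 sets the cut-off: a score of 14 or less is lower literacy. Late in the study, a patient whose literacy level is over quota at that site becomes ineligible.

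**The concern.** Concealment requires that whoever decides on entry and stratum cannot know the next arm. A secure website controls who can log in. It does not hide the next entry from an RA who is authorised to log in. An article may leave block size or software to a fuller document. Here, however, it fixes a mechanism, and that mechanism as worded puts sequences, not single assignments, in front of the enrolling staff.

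Two routes to bias follow. Knowing the next arm, an RA could press on with or drop a particular patient. The RA could also let the next arm influence the scoring of a borderline literacy test, which decides the stratum and, once quotas bind, eligibility. Literacy is a factor in hypotheses HA1 and HA2 of both primary aims, so the second route would reach the interactions under test as well as the effect of delivery mode. The intention-to-treat analysis in the primary aims section does not correct selection that happens before assignment.

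A second, smaller matter is that equal arms are promised within site, while the sequences are described only by language and literacy. The two sentences leave open whether site is a stratification factor.

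**Working it through.** **The plan's own figure.** Eight cells (mode × language × literacy) of 150 give 8 × 150 = 1200, which matches the sample size section. So do 4 sites × 300 = 1200, and Table 3's 1000 × 1.20 = 1200 and 800 × 1.25 × 1.20 = 1200. No sample size changes because of this point.

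**Who controls what before assignment**

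| Step | Who | Where |
|---|---|---|
| Order of approach | computer-generated random list of rooms | Enrollment |
| Potential and in-person eligibility | RA | Enrollment |
| SAHL-S&E, cut-off 14, sets stratum | RA | Enrollment; Table 2 |
| Pre-information knowledge | patient, automated telephone keypad | Pre-information delivery questionnaires |
| Arm | RA consults posted sequences | Information delivery |

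No section says that only one entry is shown, that an arm is released only after registration, or that later entries are hidden.

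**How much could be foreseen.** If the list is readable as posted, 100% of next arms are known. For comparison, suppose arms are released one at a time but the block size is fixed and known and past arms are seen. With block size 2m and 1:1 allocation:

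- Expected share guessed correctly = {m + ½[2^(2m)/C(2m, m) − 1]} / (2m)
- Share known with certainty = 1/(m + 1)

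| Block size | Guessed correctly | Known with certainty |
|---|---|---|
| 2 | 1.5/2 = 75% | 50% |
| 4 | 2.833/4 = 71% | 33% |
| 6 | 4.1/6 = 68% | 25% |
| 8 | 5.329/8 = 67% | 20% |

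The article gives no block size, so 2 to 8 is an assumed range. Pure chance is 50%.

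**What a given bias would do (illustration only).** Table 3 gives an SD of about 3 and a short-term within-person correlation of 0.7. The SD of the change score is 3 × √[2 × (1 − 0.7)] = 2.32. With 600 per arm, the standard error of the arm difference is 2.32 × √(2/600) = 0.134. With no true difference and selection bias b, the two-sided rejection rate at 0.05 is Φ(b/0.134 − 1.96) + Φ(−b/0.134 − 1.96):

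- b = 0.1 points: about 12%
- b = 0.2 points: about 32%
- b = 0.3 points: about 61%

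These values of b are assumptions. Nothing in the article gives the actual bias.

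**Site wording.** Language × literacy gives 2 × 2 = 4 sequences. Each site is planned to recruit one language, so sequences within site and literacy would number 4 × 2 = 8. Only the second arrangement guarantees balanced arms at each site. The article's wording fits either.

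**How much enrolment remains.** The sample size section reports 1165 participants past the three-month follow-up. Against 1200 this leaves 35, or 35/1200 = 2.9%. Those who miss the three-month follow-up are replaced, so the number already randomised may exceed 1165.

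**The case against.** The strongest reply is that the central fact is inferred. The article names a central computerised system and says that RAs consult the website at the point of assignment. Both are compatible with a page that shows one arm at a time. This stands, and it rules out the stronger reading that allocation was not concealed. A reader might infer that from the word sequences, but the article never says that entries beyond the current one are visible.

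Safeguards also exist. Rooms are approached in a random order set before each shift. The SAHL-S&E has 18 items, a fixed cut-off and a data recorder, so moving a patient across the cut-off would mean mis-scoring it. Pre-information knowledge is collected by an automated system, and Aim 1 analyses change from it. The order described already puts literacy scoring and pre-information questionnaires before assignment. These features reduce the risk. They do not remove it, because no lock is stated and a posted list can be consulted earlier.

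A reader might also take this sentence as RA discretion over timing: "If the reason can be overcome (e.g., waiting for a radiograph), the RAs will accommodate the request, and will proceed with screening or participation". It concerns patients who decline or break off, whose reasons are recorded, so the pause is at the patient's request.

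A reader might infer that two sites necessarily share a list and that the promised balance must fail. The explicit promise of balance by site makes this only an ambiguity.

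Finally, it is tempting to size the bias by setting the 2.4-point literacy difference in the earlier Spanish-language trial (Background) against the 0.75-point interaction step in Table 3. The first is an adjusted difference in post-information level and the second concerns improvement. Any share of misplaced patients would be invented, and patients near the cut-off probably differ by less than the whole groups do. That comparison should not be used.

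**Conclusion.** The point holds as a fault in the procedure as described. Sequences are posted for the staff who screen patients and determine stratum, and no stated step prevents foreknowledge. Concealment is therefore not assured, and selective enrolment or arm-dependent stratum placement is possible. The article does not show that either occurred.

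Foreseeability is 100% if the posted list can be read ahead, and about 67% to 75% under single release with known fixed blocks of 2 to 8. The direction and size of any bias cannot be derived from the article. The rejection rates above show only that a bias of a few tenths of a point would matter at this sample size. The mismatch over site is an ambiguity to be reconciled.

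**What to change.** **For any remaining or replacement enrolment:** replace the posted sequences with central release of a single arm per request. Release should follow only after eligibility, SAHL-S&E score and stratum, and pre-information questionnaires are entered and locked. Block sizes should vary and be withheld from RAs. This takes a small configuration change and one protocol sentence, but it can affect only the small part of the sample still to be recruited.

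**In the text:** state whether each site has its own sequence, so that the promise of balance by site and the description of the sequences agree.

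**For participants already randomised**, where most of the remedy lies:

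- State whether RAs could view future assignments, and how block sizes were handled. If arms were in fact released singly after registration, one corrected sentence settles the concealment question.
- Report arm balance of SAHL-S&E scores near the cut-off, of pre-information knowledge, and by site.
- If access logs exist (the article mentions none), report website access times against screening times.
- If future arms were visible, disclose this as a limitation.

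The cost is modest extra analysis and reporting. No additional patients are needed.
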